**Demographic variables**
Age ≤ 40 years versus > 40 years
Women versus men
High education versus low education

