## Methods/Design

We designed an observer and patient blinded randomised cost-effectiveness trial in the treatment of cervical disc herniation in which three surgical techniques are compared in a parallel group design. Adjacent level disease will be used as primary outcome measure and NDI as secondary outcome. As such we will evaluate the clinical appropriateness and superiority of disc prosthesis on one hand, cervical fusion on the other hand, and compare this to discectomy without any implant. The follow-up period will last 5 years.

In order to collect enough patients, a multicenter design is necessary. The clinical centers that are planned to recruit patients into the NECK trial are: Medical Center Haaglanden, The Hague; Leiden University Medical Center; University Medical Center Groningen; Medical Center Alkmaar; and University Medical Center Maastricht. The protocol was approved by the ethics committee/IRB in each participating hospital.

The primary question of the NECK trial is whether ACDP has a lower incidence of symptomatic adjacent disc degeneration compared to ACD and ACDF. Symptomatic adjacent level disease is defined as development of new symptoms (i.e. neck pain, radiculopathy, or myelopathy) referable to a motion segment adjacent to the site of the previous anterior surgery. In addition, we want to identify certain subgroups that may benefit more of one of the allocated treatments.

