**Inclusion criteria**
Age 18 - 65 years
Radicular signs and symptoms in one or both arms
At least 8 weeks prior conservative treatment
Radiographic diagnosis of cervical disc herniation and/or osteophyte at 1 level (C3-C4 to C7-T1) in accordance with clinical signs and symptoms
Informed consent

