### Baseline data

Baseline assessment includes demographics, hobbies, sports, work status, smoking status, neck and arm pain history of patient and family, medical history and co-morbidity, body mass index, and neurological signs and symptoms. The patient's satisfaction at work will be registered. The treatment preference of patient, surgeon and research nurse will also be assessed.

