### Data Analysis

The data will be analysed according to the stopping rules, i.e. after approximately 1.8, 2.6 and 3.2 years under H0 and 2.2, 3.2 and 4.2 years under H1. The actual analysis times depend on the number of events observed (15, 30 and 45). This establishes an answer to the main objectives in terms of the comparison of ADCF to ADCP. Long-term analyses of all results will be conducted irrespective of an early achievement of futility or efficacy establishing a comparison at 52, 104, 156, 208 and 260 weeks. However, these analyses will be performed after the final analysis of the trial has reached the conclusion of efficacy or futility. For all analyses, assessments performed at the first outpatient visit will be taken as baseline. Baseline comparability will be analysed by descriptive statistics to determine whether randomisation was successful. Baseline measurements will be used as covariates in the analyses to increase power. Differences in outcome measures between the 2 pairs of groups, together with 95% confidence intervals, will be calculated. All data are analysed according the "intent-to-treat principle".

The primary research objective will be tested using two likelihood ratio tests for the hazard ratio's, one for the comparison to ACD and one to ACDF. In case of homogeneity of effects, a pooled effect (adjusting for interbody fusion) will be reported. Otherwise the two analyses will be reported separately. The secondary outcome continuous measures will be compared using two t-tests in the same way (or non-parametric counterparts in case of non-symmetrical or distributions with outliers), possibly after transformations of skewed distributions.

On the other hand, repeated measurements analyses of variance for the secondary outcome measures (the continuous outcome scales) will also be performed in order to compare the evolving patterns over time.

In addition, an explorative subgroup analysis is conducted to investigate whether the treatment effect varies over specific subgroups of patients (Table 4).

**Table 4 T4:** Selected prognostic variables for subgroup analysis.

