**Anamnestic and neurological variables**
Neck pain versus no neck pain
Quetelet index ≤ 30 versus > 30

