**Radiological variables**
Uncovertebral osteophytes versus no osteophytes
Straight neck versus lordotic neck
Low disc (≤5 mm) versus high disc (>5 mm)

Data will be stored via the internet-based secure data management system "ProMISe" of the department of Medical Statistics and Bio Informatics[39]. The analyses will be carried out using appropriate statistical software (e.g. SPSS).

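### Table 4 reduces age, Quetelet index and disc height to two-way cuts for the exploratory subgroup analysis; continuous interaction terms would use the data better (optional change)

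*Protocol article*

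**What the plan says.** The Methods/Design section of the protocol article follows its primary question with a further aim: "we want to identify certain subgroups that may benefit more of one of the allocated treatments". The Background section says much the same. Under Data Analysis the method is described as follows: "an explorative subgroup analysis is conducted to investigate whether the treatment effect varies over specific subgroups of patients". Table 4 then lists the subgroups.

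Three entries split a measured quantity:
- "Age ≤ 40 years versus > 40 years"
- "Quetelet index ≤ 30 versus > 30"
- disc height, divided into low and high at 5 mm.

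No reason is given for any cut, and no continuous version is mentioned. No interaction test, interaction effect size or interaction power is stated.

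On what is recorded:
- Age limits are given in years ("Age 18 - 65 years").
- The Baseline data section includes "medical history and co-morbidity, body mass index, and neurological signs and symptoms".
- Disc height in mm is in neither the Baseline data section nor the Radiographic evaluation section. The 5 mm cut and the exclusion of very narrow discs (central height under 3 mm) both imply that it is measured.
- Table 4 also lists "Neck pain versus no neck pain", while VAS neck pain is scored separately at the research nurse intake.

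**The concern.** Whether benefit varies with age, body mass index or disc height is a question about a gradient. A two-way cut treats everyone on one side as identical, so a patient aged 41 counts the same as one aged 65. If the treatment effect changes gradually, the cut discards part of the information about that change. Interaction analyses usually have little power to begin with, so a real gradient becomes easier to miss. This bears on a question that the article names as an aim, and for at least two of the three modifiers the finer data are already in hand.

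**Working it through.** **Is there a figure to reproduce?** The article states no interaction power. Its main-effect chain does reproduce: ln(0.98)/ln(0.93) = 0.278, stated as 0.28; 1.5 × 450 = 675; 675/0.90 = 750. None of this speaks to interactions.

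**Information kept by a cut.** When the effect is linear in the modifier, the efficiency of the cut relative to the continuous term is the squared correlation between the two. With p the share of patients at or below the cut and φ(z) the normal density there:
- normal modifier: φ(z)²/[p(1−p)]
- uniform modifier: 3p(1−p)

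A median cut of a normal modifier keeps 0.399²/0.25 = 64%.

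**Power after the cut**, at a two-sided 5% level: Φ(√eff × (1.960 + z_base) − 1.960). For 80% power on the full scale the bracket is 1.960 + 0.842 = 2.802.

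Two cases in full:
- Age uniform on 18 to 65: p = 22/47 = 0.468 and eff = 3 × 0.468 × 0.532 = 0.747. Power is Φ(0.864 × 2.802 − 1.960) = 68%.
- Quetelet index, mean 26, SD 4: z = 1, φ = 0.242, p = 0.841 and eff = 0.0586/0.1335 = 0.439. Power is Φ(0.662 × 2.802 − 1.960) = 46%.

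All distributions below are assumptions, because the article gives none.

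| Modifier and assumed distribution | Share at or below cut | Information kept | Power (80% on full scale) | Loss, points |
|---|---|---|---|---|
| Age, normal 45, SD 9 | 29% | 57% | 56% | 24 |
| Age, uniform 18–65 | 47% | 75% | 68% | 12 |
| Quetelet index, normal 26, SD 4 | 84% | 44% | 46% | 34 |
| Quetelet index, normal 27, SD 5 | 73% | 56% | 55% | 25 |
| Disc height, normal 5.5, SD 1.2 mm | 34% | 60% | 58% | 22 |
| Disc height, uniform 3–8 mm | 40% | 72% | 66% | 14 |

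Information lost is therefore 25 to 56%, and power lost 12 to 34 points. A simulation of linear models with 450 patients (225 per arm, 4,000 runs, age truncated to 18–65) gave 59–67% for age, 46–58% for Quetelet index and 56–64% for disc height. These agree with the table to within about 3 points.

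**Dependence on base power.** From 50% on the full scale, the same cuts leave about 25 to 40%. Across base powers of 20 to 90% and cuts from 50/50 to 10/90 (plus uniform age), the loss runs from about 4 to 43 points.

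**Primary outcome.** Data Analysis gives 45 events at the last look for fusion versus prosthesis. The SE of the log hazard-ratio change per SD is √(1/d₁ + 1/d₂). It is 0.298 with an even split. With 35 and 10 events (45 × 7/9 and 45 × 2/9, following the assumed rates of 7% and 2%) it is 0.359.
- Assumed hazard-ratio ratio of 1.5 per SD: continuous power 20 to 28%, cut power 11 to 19% (median to 15/85 cuts), a loss of about 6 to 13 points.
- Ratio of 2.0 per SD: continuous power 49 to 64%, a loss of about 15 to 31 points.
- Reaching 80% power on the continuous scale needs a ratio of exp(2.802 × SE), about 2.3 to 2.7 per SD.

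**If the effect is a true step at the cut**, the efficiencies reverse. Where the cut has 80% power, the linear term has 61% (median cut) or 45% (15/85 cut).

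**The case against.** The strongest reply is that the analysis is labelled exploratory, no test is named, and Table 4 does not rule out a continuous model alongside the cuts. The article may leave the model form to an analysis plan that is not shown. No primary or secondary treatment comparison depends on Table 4. This stands as far as severity goes. It does not remove the point, because the article does fix the form of each modifier, and that form is the less informative one for a gradual effect.

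Several stronger readings are tempting and are not supported:
- **That the trial loses a known amount of power.** The point loss rests on assumed distributions, base power and linearity. On the primary outcome, a modest interaction would probably be missed with either form.
- **That the cuts raise the risk of false subgroups.** Cuts listed in advance do not raise the type I error of an interaction test, and they prevent cut points chosen from the data.
- **That the age cut is off-centre.** The midpoint of 18 to 65 is 41.5, so 40 is nearly central in the eligible range.
- **That neck pain yes/no is a dichotomised VAS.** It stands among the anamnestic variables, and Baseline data includes neck pain history. It may be a history item, and no loss was computed for it.
- **That a spline would secure the gain.** With the noncentrality that gives 80% power on 1 df, a 2-df test has about 71% and a 3-df test about 64%. That gives back much of the advantage, and such terms would be fragile with 45 events.

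**Conclusion.** The point holds for age, Quetelet index and disc height, the last provided it is recorded in mm. Under a roughly linear change in benefit, the Table 4 cuts discard about 25 to 56% of the information on the interaction, for the distributions assumed. The corresponding power loss of about 12 to 34 points is an illustration for a continuous outcome with 80% power on the full scale. It is not a property of this trial. For the primary outcome with 45 events, power for a modest interaction is low under either form, and the absolute loss is about 6 to 13 points. The direction reverses if the effect truly steps at a cut. Severity is optional, because the analysis is exploratory.

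**What to change.** State in the analysis section or analysis plan that, for each outcome, treatment-by-modifier interaction will be assessed with age, Quetelet index and disc height (where measured in mm) as continuous linear terms. Keep the Table 4 cuts for displaying subgroup estimates, and leave the truly categorical modifiers as they are. Do not use a spline as the main interaction test.

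Baseline VAS neck pain may be added as a separate continuous modifier. It should not replace neck pain yes/no, since that would change the variable.

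The cost is a sentence of text, with no new patients or visits. The downside is the lower efficiency of a linear term under a true step at a cut; the displayed subgroup estimates would still show such a pattern.

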**Anamnestic and neurological variables**
Neck pain versus no neck pain
Quetelet index ≤ 30 versus > 30
**Radiological variables**
Uncovertebral osteophytes versus no osteophytes
Straight neck versus lordotic neck
Low disc (≤5 mm) versus high disc (>5 mm)

Data will be stored via the internet-based secure data management system "ProMISe" of the department of Medical Statistics and Bio Informatics[39]. The analyses will be carried out using appropriate statistical software (e.g. SPSS).

## Discussion

Since the introduction of anterior approach of the cervical spine by Cloward, Robinson and Smith[1], a dispute has started about the best surgical treatment. The purpose of all surgical procedures is removal of the intervertebral disc in order to decompress the nerve root and alleviate radicular pain. However, cervical instability and segmental collapse with recurrent radicular pain has been documented after anterior discectomy. For this reason, most surgeons in general hospitals perform anterior discectomy with interbody fusion while most academic surgeons perform a discectomy *sec *as a result of lack of evidence. The results of various randomised trials suggest that interbody fusion may not be necessary in all cases[3-9]. In fact, The Cochrane Review even mentioned advantages of anterior discectomy only; lower costs, shorter operation time and faster return to work[10].

One of the main drawbacks of arthrodesis of a motion segment is increased load and stress at the levels adjacent to the fusion site. The concept of accelerated adjacent disc degeneration (AADD) is widely discussed. Hilibrand et al. reported a large retrospective study of patients who underwent anterior discectomy with fusion. Symptomatic adjacent level degeneration occurred at a relative constant incidence of 2.9% annually[11]. However, data on asymptomatic patients suggest that intervertebral disc degeneration is a physiological process, which may be accelerated by interbody fusion[40,41].

The rationale of artificial disc replacement, mainly industry driven, is motion preservation with subsequent prevention of adjacent disc degeneration. Various prospective randomised trials have shown that cervical disc prosthesis is a safe and reliable alternative to cervical fusion[12-17]. Data focused on adjacent disc degeneration after arthroplasty is limited, but the incidence of AADD seems low[18,19]. In the largest randomised trial on cervical disc prosthesis by Mummaneni et al., radiographic evaluation of adjacent level degeneration was not assessed[16]. Moreover, the follow-up period in all conducted studies is too short for proper evaluation of AADD.

The primary concern on studies focused on AADD, is the low incidence of events. As outlined in our sample size calculation, 750 patients will need to be randomised to elucidate the dispute on prevention of AADD in disc arthroplasty studies. In addition, an extra treatment arm of anterior discectomy without fusion will be needed to justify the high costs of cages or disc prostheses. Bartels et al. have published a similar protocol on cervical disc herniation in which 3 surgical strategies are compared[42]. However, the NDI was taken as primary outcome measure. Therefore, in our opinion, the number of patients enrolled is not enough for scientific proof of possible reduced incidence of AADD after disc arthroplasty.

The NECK trial is designed to demonstrate the effectiveness and security of cervical disc prosthesis, focused on adjacent segment degeneration and functional outcome. ACDP will be randomly and blindly compared with ACD and ACDF. The only way to elucidate the dispute on AADD prevention, is a 3 arm randomised trial with large number of patients to be included. As such we will evaluate the clinical appropriateness and superiority of disc prosthesis on one hand, cervical fusion on the other hand, and compare this to discectomy without any implant.

## Abbreviations

NECK: netherlands cervical kinematics; ACD: anterior cervical discectomy; ACDF: anterior cervical discectomy with fusion; ACDP: anterior cervical discectomy with prosthesis; NDI: neck disability index; VAS: visual analogue scale; AADD: accelerated adjacent disc degeneration; MRI: magnetic resonance imaging; CT: computed tomography; HADS: hospital anxiety depression scale.
